**Fig. 3 Fig3:**
[figure not shown]
Overview on the anabolic interventions in the longitudinal phase of TEMPUS-FUGIT. Each group will receive 800 International Units (IU) of vitamin D

In addition to the two fecal samples delivered during the preparation period, sarcopenic participants will be requested to deliver an additional fecal sample and to complete a medical and the ROME IV questionnaire at week 4, week 8 and week 12 of the intervention period. At weeks 1, 4 and 8 additional non-fasted blood samples will be taken to assess clinical parameters. Also axillary body temperature, blood pressure, length, height and waist and hip circumference will be determined at these timepoints. At week 12, muscle mass, strength, physical performance, QoL, nutritional status and cognitive performance will be assessed using the same testing program as performed during the baseline visit. A complete overview of all the study procedures and a timetable is given in Table 1.

**Table 1 Tab1:** Study procedures and timeline

Study week (W)	All participants			Sarcopenic participants						
	Screening	Preparation	Baseline	Intervention period						
				W1	W2	W4	W6	W8	W10	W12
Fecal sample, MQ^m^ and ROME IV^n^ questionnaire		✓				✓		✓		✓
Eligibility criteria, informed consent, alcohol intake, smoking, educational and marital status	✓									
Muscle strength (Biodex), muscle mass^a^ (DXA, BIA), SPPB^b^, BMI^c^			✓							✓
Physical activity by IMU^d^		✓	✓	✓	✓	✓	✓	✓	✓	✓
Exercise compliance^d,e^ and MiniBesTest^d,e^			✓	✓	✓	✓	✓	✓	✓	✓
SF-36^f^ and SarQol^g^, ADL^h^, frailty^i^, Short-FES-I,^j^ cognitive test battery^k^			✓							✓
Food diary analyses to assess associations between GM and habitual protein intake		✓		✓		✓				✓
Falls, health care use			✓	✓	✓	✓	✓	✓	✓	✓
MNA-SF^l^			✓				✓			✓
Body temperature, waist & hip circumference, blood pressure, weight, length			✓			✓		✓		✓
Blood sample	✓		✓	✓		✓		✓		✓

^a^:assess muscle mass with Dual X-ray Absorptiometry and Bio-electrical Impedance Analysis

^b^:Short Physical Performance Battery

^c^:Body Mass Index

^d^:assess physical activity level by movement monitor

^e^:only participants in the exercise group

^f^:SF-36 health related quality of life scale questionnaire

^g^:SarQol questionnaire

^h^:Barthel index to assess Activities of Daily Living (ADL)

^i^:frailty defined according the Fried criteria

^j^:Short Falls Efficacy Scale international

^k^: cognitive tests comprising: Repeatable Battery for the Assessment of Neuropsychological Status (RBANS), Trail-Making-Test (TMT) part A and B, Maze test, Stroop test

^l^:Mini nutritional assessment short form

^m^: general medical questionnaire

^n^: questionnaire to screen for Irritable Bowel Syndrome (IBS)

### Outcome measurements

For the cross-sectional phase, outcome measurements will be taken at the baseline test visit.The primary outcomes in this phase are:Differences in multiple GM α-, and β-diversity indices, enterotypes, bacterial cell counts and abundance of specific taxa between sarcopenic older adults and non-sarcopenic controls using two fecal samples collected in each group at the baseline test visit [52, 53]. Both GM diversity indices and measures for expression of bacterial abundance will be specified in the section “Assessment of GM composition and statistical analyses” further below.Differences in the levels of the intestinal inflammatory markers fecal calprotectin, lactoferrin and S100A12 between sarcopenic older adults and non-sarcopenic controls using two fecal samples collected in each group at the baseline test visit.Secondary outcomes assessed in sarcopenic older adults are:Associations between GM composition and clinical parameters: 1) ALM (by whole body DXA and BIA), muscle strength (HGS, CST and knee strength) and physical performance (gait speed and SPPB); 2) protein intake by four-day food diaries and risk of malnutrition by the MNA-SF.Associations between GM and levels of systemic (hs-CRP; IL4, IL6, IL-13, IL-1β, TNF-α, and creatin kinase) and intestinal (fecal calprotectin, lactoferrin and S100A12) inflammatory markers.Associations between levels of systemic and intestinal inflammatory markers.Associations between fecal calprotectin, lactoferrin, S100 and respectively: 1) aforementioned systemic inflammatory markers; 2) ALM (whole-body DXA), muscle strength (HGS, CST, knee strength) and physical performance (gait speed, SPPB); 3) systemic muscle biomarkers (myostatin, activin A, irisin, apelin).

For the longitudinal phase in sarcopenic participants, outcome measurements will be collected from the baseline test visit until the week 12 visit. The primary outcome of this phase is:Change in GM composition between the protein intervention group (group B, Fig. 3) and the placebo group (group E).

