The Trial in Elderly with Musculoskeletal Problems due to Underlying Sarcopenia-Faeces to Unravel the Gut and Inflammation Translationally (TEMPUS-FUGIT) aims to unravel the gut-muscle axis in age-related sarcopenia by addressing these gaps. First, TEMPUS-FUGIT will compare GM composition and intestinal inflammation between a well-defined sarcopenic community-dwelling older population and non-sarcopenic controls. Second, in sarcopenic individuals, associations between sarcopenia-defining parameters and GM, systemic and intestinal inflammation, that all may contribute to sarcopenia, will be explored. An overview of the associations that will be investigated is given in Fig. 1. Finally, TEMPUS-FUGIT will explore the effects of optimized and individualized anabolic treatments for sarcopenia on the GM composition and intestinal inflammation in older persons with sarcopenia. We hypothesize a significant effect of these anabolic interventions on the GM composition in sarcopenic persons.

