### Study procedures

#### Screening visit

TEMPUS-FUGIT starts with a screening visit, where study procedures will be explained, eligibility criteria will be checked and informed consent will be obtained by one of the researchers. If the participant qualifies for the study, weight (SECA, model no 8801321009, SECA UK Ltd.) will be measured to the nearest 0.1 kg and height (Harpenden stadiometer Holtain Ltd., Crosswell UK) to the nearest 0.1 cm, measured barefoot, standing upright with clothes on. BMI is calculated through weight/height^2^ (kg/m^2^). Hand grip strength (HGS) will be measured with a handheld dynamometer (Jamar 1, TEC Inc., Clifton, NJ, USA) while the participant is seated, holding the arm in a 90° angle. According to the Southampton protocol, HGS is measured six times for alternating hands and the maximal value is reported [32, 33]. The chair stand test (CST) determines leg muscle strength by measuring the time it takes for the participant to rise five successive times out of a chair as fast as possible without using any support and holding the arms crossed in front of the chest. Cut-off values for low muscle strength according to EWGSOP2 (and, hence, probable sarcopenia) are > 15 s for the CST for both sexes and a HGS < 27 kg and < 16 kg for men and women respectively [5]. Finally, when no recent lab results (12 weeks old) are available, an additional fasted sample will be taken in order to check whether the participants fasted glucose levels are < 126 mg/dl or HbA1C < 6.5%, to exclude diabetes mellitus [34].

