#### Preparation period

When the participant is diagnosed with at least probable sarcopenia based on the EWGSOP2-defined low muscle strength and meets the inclusion criteria, the participant is eligible for both the cross-sectional phase and the longitudinal phase of TEMPUS-FUGIT.

For the longitudinal phase, the sarcopenic participants will be 1:1 block randomized into one of the five intervention groups, as previously described by Dedeyne et al. [29]. All these participants will be requested to take 800 International Units (IU) of vitamin D and one capsule of omega-3 PUFA/placebo per day, starting one month before the baseline test visit. Participants will also be asked to keep a food diary during four non-consecutive days in order to individually supplement protein intake until the recommended daily allowance (RDA) for older adults with chronic conditions (i.e., 1.5 g/kg BW/day) [35]. Furthermore, these food diaries will be analyzed to obtain the participants’ habitual protein and energy intake, and to assess possible associations with GM composition. Five days prior to the baseline test visit, participants will be requested to start to take their individualized protein supplements or placebo powder and will wear an inertial measurement unit (IMU) (MoveMonitor + , McRoberts, The Netherlands) to monitor physical activity. Participants will be requested to register the intake of the vitamin D, omega-3/placebo and protein/placebo supplement in a trial diary during the intervention. In the week prior to the baseline test visit, participants need to collect two fecal samples produced at two separate moments with the provided material (Laboratory of Molecular Bacteriology, KU Leuven/Rega Instituut, Vlaams Instituut voor Biotechnologie (VIB), Belgium). Immediately after sample collection, the participant fills out the Bristol Stool Score Chart [36] to determine fecal consistency and preserves the samples at -20°C [37]. Finally, participants will be requested to complete a general health questionnaire as well as the ROME IV questionnaire to screen for IBS symptoms [38].

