#### Baseline test visit

For both the non-sarcopenic controls and the sarcopenic participants, a test visit at the study center will follow the preparation period. During this visit, the four-day food diary, the IMU and the two frozen fecal samples brought along by the participant (avoiding thawing using ice packs) will be collected and fasted blood samples will be taken.The fecal samples will immediately be stored at -80 °C until analysis of intestinal inflammatory markers (fecal calprotectin, lactoferrin and S100A12) and GM composition. Quantitative Microbiome Profiles (QMP) will be obtained through the following extensive -omics analysis. Targeted (16S/18S) amplicon sequencing analysis of the V3-V4 variable region of the 16S rRNA gene, via reverse polymerase chain reaction (RT-qPCR) technique will provide information about GM taxonomic composition, i.e., the type of GM present, and their abundance.. Metagenomic analysis (comprehensive assessment of DNA of the complete content of a clinical sample) will be performed through whole genome shotgun analysis using next generation platforms. Intestinal inflammatory markers will be determined through Enzyme Linked Immunosorbent Assay (ELISA).In fasted blood samples, the following parameters will be determined: systemic inflammatory parameters (hs-CRP, IL-4, IL-6, IL-13, IL-1β, TNF-α and creatine kinase), muscle markers (myostatin, activin A, irisin, apelin), clinical parameters (hemoglobin, eGFR, serum albumin, fasting glucose, red blood cell count, hematocrit, Mean Corpuscular Volume (MCV), Mean Corpuscular Hemoglobin (MCH), Mean Corpuscular Hemoglobin Concentration (MCHC), white blood cell count and formula, platelet count, hemoglobin A1c (HbA1c), ferritin, aspartate aminotransferase (AST), alanin transaminase (ALT), γ-glutamyltransferase, total and direct bilirubin, total protein, serum protein electrophoresis, uric acid, sedimentation rate, triglycerides and total, high-density lipoprotein (HDL) and low-density lipoprotein (LDL) cholesterol, and hormonal status (25-hydroxyvitamin D, vitamin B12, morning cortisol, insulin, insulin-like growth factor (IGF-1)).

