### Assessment of GM composition and statistical analyses

GM analyses will comprise determination of within sample diversity (α-diversity), including sample richness, taxa abundance, evenness, and taxa distribution through the following indices: Chao 1, Shannon and Simpson’s indices, abundance-based coverage estimators (ACE) index and the Good’s Coverage index. Taxa abundance will be expressed as Operational Taxonomic Units (OTU) and/or Amplicon Sequence Variants (ASV). Sequencing reads will be demultiplexed with LotuS (version 1.565) and processed further with the DADA2 pipeline (version 1.6.0), using the RDP classifier version 2.12 for taxonomy assignment (default parameters). Between sample dissimilarity (β-diversity) will be determined with Bray–Curtis dissimilarity (through a distance based non-parametrical permutational analysis of variance (PERMANOVA) test) and weighted and unweighted UniFrac (through principal coordinates analysis (PCoA)), respectively. Comparisons of relative GM abundance between sarcopenic and non-sarcopenic older adults will be performed through linear discriminant analysis (LDA) effect size (LEfSe). GM analyses, as well as visualization of the results will be performed using R vegan and phyloseq packages [54]. Enterotyping (or community-typing) will be performed based on the Dirichlet-multi-nominal Model (DMM) approach in R (dmn function) as previously described on a combined genus-level abundance matric containing the study samples as well as 1106 Flemish Gut Flora Project (FGFP) samples to increase accuracy [55, 56]. Continuous data will be checked for normality with the Shapiro–Wilk test. The t-test will be performed for between-group analysis of continuous clinical parameters, if normally distributed. For GM analyses, non-parametric testing will be applied. The Mann–Whitney U test will be performed in case of non-parametric distribution. Correlations between microbiota species and clinical parameters will be assessed with Spearman correlation. Linear regression models adjusted for putative confounders (e.g., age) will be used to check for associations between GM species abundance and clinical parameters. To determine possible effects of the interventions on GM in different groups, linear mixed models will be applied. Multiple testing corrections will be applied if it is applicable (Benjamini-Hochberg- False Discovery Rate (FDR)). An FDR of ≤ 0.10 will be taken into account for GM analyses [57]. Level of significance will be a p-value of ≤ 0.05. A bioinformatician from VIB and a statistician from LBiostat will be consulted for the statistical analyses.

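### Gut microbiota–strength associations are assessed only in a group selected on low strength, so null results for grip or chair stand will say little; a group-adjusted all-participant model should be added

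*Protocol article*

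**What the plan says.** The Background sets the aim: "Second, in sarcopenic individuals, associations between sarcopenia-defining parameters and GM, systemic and intestinal inflammation, that all may contribute to sarcopenia, will be explored". Outcome measurements follows it. Under "Secondary outcomes assessed in sarcopenic older adults are" it lists associations of GM with "ALM (by whole body DXA and BIA), muscle strength (HGS, CST and knee strength) and physical performance (gait speed and SPPB", with protein intake and nutritional risk, and with systemic and intestinal inflammatory markers. It also lists associations of the faecal markers with the muscle and systemic measures.

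Entry to the sarcopenic group rests on strength. The Preparation period section begins "When the participant is diagnosed with at least probable sarcopenia based on the EWGSOP2-defined low muscle strength", and the Screening visit section gives the "Cut-off values for low muscle strength according to EWGSOP2": CST above 15 s, or HGS below 27 kg (men) or 16 kg (women).

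Controls are measured as well: "For both the non-sarcopenic controls and the sarcopenic participants, a test visit at the study center will follow the preparation period". That visit covers two faecal samples, fasted blood, body composition, strength and performance. In Outcome measurements the control data serve only the primary group comparisons.

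The analysis section uses Spearman correlation between microbiota species and clinical parameters, and adjusted linear regression "used to check for associations between GM species abundance and clinical parameters". It does not say which variable is the response.

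**The concern.** HGS and CST are both entry criteria and association variables. Selecting on one of two correlated variables narrows its spread and lowers the correlation, so a real GM–strength link would tend to appear weak or absent in the sarcopenic group. The Discussion wants to learn how GM and inflammation contribute to sarcopenia and to find biomarkers for people at risk. A null result from the restricted group could be taken as evidence against a gut–muscle link when the design had little chance of showing one. Meanwhile, 100 controls with the same measurements could add information to these analyses at no extra data cost.

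**Working it through.** **The plan's own figures.** No power or detectable correlation is stated for the associations. The one size figure that can be reproduced is the 110 controls: 100/(1 − 0.0588) = 106.2, so 107 are needed and 110 is enough. It has no bearing on this point.

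**Inputs from the protocol.** 100 cases and 100 controls; entry on HGS or CST; Spearman correlation; significance at 0.05; FDR 0.10 for GM analyses.

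**Assumptions, not in the protocol.** Multivariate normal data, with chair stand scored so that lower is worse; true GM–strength correlation 0.30 or 0.20 for both tests; 10–30% of the source population beyond each cut-off; correlation between the two tests 0.3–0.6; two-sided tests before FDR correction.

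**Step 1: sample size alone.** Detectable r at 80% power = tanh[(1.960 + 0.842)/√(n − 3)].
- n = 100: tanh(2.802/9.849) = 0.277
- n = 200: tanh(2.802/14.036) = 0.197

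**Step 2: truncation on a single test.** With u the ratio of the restricted to the full standard deviation, r′ = r·u/√(1 − r² + r²u²). If grip is the only criterion and 20% fall below it, u is about 0.468. Then r′ = 0.140/√(0.91 + 0.0197) = 0.146 for a true 0.30. The simulated Spearman value in this setting is about 0.13.

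**Step 3: entry on either test, as planned.** Simulation gives:

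| | True r 0.30 | True r 0.20 |
|---|---|---|
| Spearman r, whole population | about 0.29 | about 0.19 |
| Spearman r, cases only | 0.10–0.15 | 0.07–0.10 |
| Power, 100 cases | 17–31% | 10–15% |
| Power, all 200 with group term | 71–74% | 35–41% |

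For the true 0.30, the group-adjusted slope of GM on strength is 0.19–0.23. The case-only slope is 0.12–0.20, so regression inside the sarcopenic group does not escape the problem either.

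**Step 4: variables not used for selection.**
- ALM (assumed correlation 0.5 with grip and 0.3 with chair stand; true GM–ALM 0.30): case-only Spearman r falls from 0.29 to 0.20–0.22.
- GM–inflammation, with an assumed strength–inflammation correlation of −0.2: −0.29 becomes −0.25 to −0.26. With no such correlation it stays at about −0.29 to −0.30. When the signs differ, 0.29 rises to 0.33–0.36.

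For inflammation the direction of any distortion is therefore not fixed, and the dependable cost is the one in step 1.

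**Step 5: is pooling safe?** The Preparation period section has cases take vitamin D and omega-3/placebo from one month, and protein/placebo from five days, before the baseline visit. Stool is collected in the week before that visit. Controls take none of these. Suppose GM and strength are unrelated but supplementation shifts GM by 0.3 SD in cases. A pooled model without a group term then declares an association in 23–29% of trials; with the group term the rate stays at 5%.

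**The case against.** The strongest reply is that the within-sarcopenia question is deliberate: the Background states it, it is secondary and exploratory, and how GM varies with severity among cases is a legitimate target. That stands. It is a reason to keep the case-only analyses, but it does not make a null at 17–31% power informative.

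Three stronger readings are tempting, and the documents do not support them.
- A reader might infer that every listed correlation is shrunk. Selection is on strength, not on inflammation or diet, and step 4 shows no general shrinkage there.
- A reader might infer that identical control data lie unused. The measurements are the same, but only cases are supplemented before sampling, and the controls do serve the primary comparison.
- A reader might infer that pooling all 200 recovers an unbiased slope with near-certain power. Power of about 99% arises only without the group term and largely re-expresses the case–control contrast: with groups centred, the pooled correlation is only 0.18–0.20 for a true 0.30. The slope is free of selection bias only if that one predictor alone drives entry, which is not so here.

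The abstract and the analysis section name no population for the associations. In a condensed article that is not a contradiction of the Background.

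**Conclusion.** The point holds for GM and faecal markers against HGS and CST, and more weakly for related measures such as ALM. Under the stated assumptions the case-only correlation falls by roughly half to two thirds. Elsewhere the loss is mainly 100 participants instead of 200. All correlation sizes and the fractions beyond the cut-offs are assumed, and FDR correction would lower every power figure. This is a limit on efficiency and interpretation, not an internal error. Adding the group-adjusted model raises power about two- to fourfold without new data, and that justifies the change.

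**What to change.** Keep the within-sarcopenia associations as declared. In Outcome measurements and in the statistical analysis section, add a regression on all participants:
- response: the GM feature or faecal marker;
- predictor: the muscle parameter or inflammatory marker;
- adjustment: age, sex, BMI and sarcopenia group;
- further terms: a group-by-parameter interaction and an indicator for pre-baseline supplement assignment (coded arm labels would keep the statistician blinded).

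State that a pooled model without the group term will not be used for inference. Name the population of each association analysis wherever it is described. When null HGS or CST associations are reported, give range restriction as a limitation, because the group-adjusted slope is still attenuated.

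The cost is some wording and a little more analysis; no new measurements are needed.

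### Associations between absolute microbiota abundance and faecal markers from the same stools can be inflated by shared water content, and the recorded Bristol score has no stated role in adjusting for it

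*Protocol article*

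**What the plan says.** All references are to the protocol article.

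- **Outcome.** Outcome measurements lists, as a secondary cross-sectional outcome in sarcopenic participants, associations between gut microbiota and systemic and "intestinal (fecal calprotectin, lactoferrin and S100A12) inflammatory markers".
- **Same material for both assays.** Under Preparation period, "participants need to collect two fecal samples produced at two separate moments with the provided material". Under Baseline test visit, these samples are kept frozen "until analysis of intestinal inflammatory markers (fecal calprotectin, lactoferrin and S100A12) and GM composition". No split of the stools by assay is described.
- **Absolute scale.** Baseline test visit states that "Quantitative Microbiome Profiles (QMP) will be obtained through the following extensive -omics analysis". Bacterial cell counts appear among the primary outcomes, and the Discussion presents quantitative profiling as a strength. The markers are measured by ELISA. No unit (wet or dry gram) is given for either side.
- **Stool consistency.** After each collection, "the participant fills out the Bristol Stool Score Chart [36] to determine fecal consistency".
- **Analysis.** Assessment of GM composition and statistical analyses names Spearman correlation, then "Linear regression models adjusted for putative confounders (e.g., age) will be used". The Abstract assigns linear regression to associations between gut, inflammatory and sarcopenia parameters. The Bristol score is not mentioned, and nothing says how the two stools are combined. Multiplicity is handled by Benjamini-Hochberg at an FDR of 0.10.

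**The concern.** A concentration per wet gram depends on how much water the gram contains. A loose stool lowers both the bacterial count and the marker level, and a dry stool raises both. If both quantities are on that scale, they share a factor unrelated to any link between microbiota and inflammation, and that factor pushes their correlation upwards.

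The push has the same sign for every taxon on the absolute scale and for all three markers. FDR control limits chance findings under a true null. It does not correct a bias that moves many tests the same way.

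The Discussion says that the link between intestinal inflammation and microbiota has, to the authors' knowledge, not been studied before. A cluster of positive associations created by water content could therefore be reported as a new biological result.

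**Working it through.** The plan gives no figure on this point, so there is none to reproduce.

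**Inputs from the article:** 100 sarcopenic participants, two baseline stools each, significance level 0.05 (taken as two-sided).

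**Assumed inputs (the article gives none), on the log scale:**
- SD of stool density *s* = 0.3
- share of density variance that persists within a person *ρ* = 0.3 to 0.5
- SD of total count *t* = 0.4, or of a taxon *t* = 0.8
- SD of a marker *m* = 1.0
- 70% of count and marker variance stable within a person, so a two-stool mean keeps 0.7 + 0.3/2 = 0.85 of it
- true association zero

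**Model.** Observed count = G + d and observed marker = H + d, with G and H independent and d the shared log density.

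**Step 1, one stool.** r = s² / √((t² + s²)(m² + s²)).
- Total count: 0.09 / √(0.25 × 1.09) = 0.172
- Taxon: 0.09 / √(0.73 × 1.09) = 0.101

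The chance of rejection is Φ(z − 1.96) + Φ(−z − 1.96), with z = atanh(r) × √97. This gives 40% and 17%.

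**Step 2, mean of two stools.** Averaging removes half of the stool-to-stool part of the density variance, leaving D = s²(ρ + (1 − ρ)/2). Then r = D / √((0.85t² + D)(0.85m² + D)).

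| | ρ | D | r | Rejection |
|---|---|---|---|---|
| Total count | 0.3 | 0.0585 | 0.0585/√(0.1945 × 0.9085) = 0.139 | 28% |
| Total count | 0.5 | 0.0675 | 0.0675/√(0.2035 × 0.9175) = 0.156 | 34% |
| Taxon | 0.3 | 0.0585 | 0.0585/√(0.6025 × 0.9085) = 0.079 | 12% |
| Taxon | 0.5 | 0.0675 | 0.0675/√(0.6115 × 0.9175) = 0.090 | 14% |

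Simulated Spearman tests at ρ = 0.3 gave 26–27% for total count and 11% for the taxon. Formula and simulation together give about 26–34% and 11–15%.

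**Step 3, sensitivity to the assumptions.** With count and marker values treated as fully stable within a person, two-stool means give:
- 29% (27% simulated) for count SD 0.5, marker SD 0.8, density SD 0.3, ρ = 0.5
- 6% for SDs of 0.7, 1.0 and 0.2 with ρ = 0.3
- 99% for SDs of 0.4, 0.5 and 0.4 with ρ = 0.7

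The direction is firm and the size is not.

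**Step 4, possible remedies, simulated with no true association unless stated.**
- *Relative abundance or dry-mass correction:* rejection returns to about 5%.
- *Adjustment for the Bristol score:* total count falls from 27% to 8–17%, depending on how well the score is assumed to track water content. Almost no power is lost.
- *Cross-stool pairing (microbiota from one stool, markers from the other):* the spurious correlation is multiplied by ρ. For total count, 0.3 × 0.172 = 0.052 (8%) and 0.5 × 0.172 = 0.086 (14%). Simulation over the assumptions tried gave 8–18%. Power for a true association falls from about 80% to 65% when one direction is used.

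**The case against.** **The unit is not stated.** If either side is corrected for dry mass, the artefact disappears, and normalisation is laboratory detail that an article may leave out. This stands, so the point is conditional.

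**The reach is narrow.** Cell counts are listed only for the comparison of sarcopenic and control groups. The association outcome says only microbiota, and proportion-based measures do not change with dilution. A reader might infer that all microbiota–inflammation results are compromised. The documents do not support that: only absolute-scale associations are exposed. These are still foreseeable, because quantitative profiling is promoted as a strength.

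**The confounder list is open.** Age is only an example, and an analysis plan that is not shown may name stool consistency. A reader might infer that the plan rules out adjustment, but it does not. What remains is that the section names an unadjusted correlation and gives no role to a covariate that the study collects for each sample.

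**Larger figures can be produced.** The one-stool formula with density SD 0.2–0.35, taxon SD 0.8–1.5 and marker SD 0.8–1.0 gives 14–76% for total count and 6–36% for taxa. The article states that both samples are used for the primary comparisons. If the associations follow suit, the lower two-stool figures apply.

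**Two stools might seem to cure the problem.** They do not. Both come from the same week, and cross-pairing leaves whatever consistency is habitual to the person. At ρ = 1 it gains nothing.

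**Adjustment can over-correct.** If gut inflammation itself loosens stool, the Bristol score carries part of the real effect. This stands as a caution on interpretation.

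Whether the Bristol chart is repeated at weeks 4, 8 and 12 is missing detail and not part of this point.

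**Conclusion.** The concern holds for absolute-scale microbiota measures set against faecal markers from the same stools, provided that both are per wet gram. Under the assumed spreads, a nominal 5% test with no true association rejects in about 26–34% of cases for total count and 11–15% for a taxon with log SD 0.8. Every SD and every within-person share behind these figures is an assumption, and the article cannot settle the true size.

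This is a secondary outcome in a study that calls itself exploratory, and no figure in the article is wrong. The point is a worthwhile, low-cost improvement to the analysis section and does not threaten the design.

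**What to change.** In Assessment of GM composition and statistical analyses:

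1. State whether quantitative abundances and faecal markers are per wet or dry gram.
2. For absolute-scale microbiota versus faecal-marker associations, adjust for the sample's Bristol score, by partial Spearman correlation or as a covariate in the planned regression. Say how the two samples and their scores are combined.
3. Report two sensitivity analyses: the same associations on relative abundance, and a cross-stool pairing in both directions with the two results averaged. The averaged correlation is not an ordinary Spearman coefficient, so its p-value should come from permuting participants.

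The cost is a few sentences, with no new samples, assays or visits. The Bristol score is a noisy proxy, so some inflation will remain, and it may absorb real signal if inflammation loosens stool. Cross-stool pairing reduces the artefact without removing it and loses power, so it should not replace the main analysis. The choice should be fixed before results are seen, because a pairing or adjustment chosen afterwards would itself be selective.
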